## Abstract

**Background:**

Pneumonia is a leading cause of childhood mortality globally. Oxygen therapy improves survival in children with pneumonia, yet its availability remains limited in many resource-constrained settings where most deaths occur. Solar-powered oxygen delivery could be a sustainable method to improve oxygen delivery in remote areas with restricted access to a supply chain of compressed oxygen cylinders and reliable electrical power.

**Methods/Design:**

This study is a randomized controlled trial (RCT). Solar-powered oxygen delivery systems will be compared to a conventional method (oxygen from cylinders) in patients with hypoxemic respiratory illness. Enrollment will occur at two sites in Uganda: Jinja Regional Referral Hospital and Kambuga District Hospital. The primary outcome will be the length of hospital stay. Secondary study endpoints will be mortality, duration of supplemental oxygen therapy (time to wean oxygen), proportion of patients successfully oxygenated, delivery system failure, cost, system maintenance and convenience.

**Discussion:**

The RCT will provide useful data on the feasibility and noninferiority of solar-powered oxygen delivery. This technological innovation uses freely available inputs, the sun and the air, to oxygenate children with pneumonia, and can be applied “off the grid” in remote and/or resource-constrained settings where most pneumonia deaths occur. If proven successful, solar-powered oxygen delivery systems could be scaled up and widely implemented for impact on global child mortality.

**Trial registration:**

Clinicaltrials.gov registration number NCT0210086 (date of registration: 27 March, 2014)

## Background

Pneumonia is a leading cause of pediatric mortality globally, causing 0.9 million deaths/year [1]. Countries in Africa and Asia report two to 10 times more cases of pneumonia than industrialized countries like the USA, and the majority of pneumonia deaths [2–4]. Respiratory distress and hypoxemia are presenting features of life-threatening bacterial pneumonia, as well as pulmonary tuberculosis, sepsis and severe malaria. These common and treatable infections lead to hypoxemia as a final common pathway, for which oxygen (O_2_) therapy is an essential supportive therapy.

Large gaps remain in the case management of children presenting to African hospitals with respiratory distress, including supplemental oxygen. A 2012 survey found that only 44 % of 231 health centers, district hospitals, and provincial/general hospitals in 12 African countries had access to oxygen on a continuous basis [5]. In Malawi in 2008, oxygen was not available in four out of five district hospital pediatric wards visited, and health workers did not know when or how to administer oxygen to children [6]. Similarly, in another survey, oxygen was not available for 13 % of hypoxemic children admitted to five hospitals in New Guinea [7]. However, improved oxygen delivery systems can lead to measurable improvements in survival. A multihospital effectiveness study in Papua New Guinea demonstrated a reduction in mortality from childhood pneumonia from 5.0 % to 3.2 % (35 % reduction in mortality) after implementation of an enhanced oxygen delivery system (pulse oximetry, oxygen concentrators and training) [8].

Current methods commonly used to deliver hospital oxygen in resource-limited settings include compressed oxygen cylinders and oxygen concentrators. Cylinders require a reliable supply chain linking the oxygen production plant to the hospital, which may be compromised by poor road conditions, costs of transportation and weak stock management. Furthermore, while cylinders themselves are robust, tank regulators, used to deliver a constant and metered flow of oxygen, are frequently ill fitting and poorly maintained, resulting in substantial gas leak and waste of compressed oxygen. Oxygen concentrators represent a significant technological advance, purifying oxygen from ambient air through selective adsorption of nitrogen using aluminum silicate sieve beds. However, these require a constant uninterrupted electrical supply, which may not be available in resource-poor settings. We propose a novel strategy for oxygen delivery that could be implemented in remote locations with minimal access to oxygen cylinders or an electrical power supply: solar-powered oxygen (SPO2) delivery. Here, we describe the protocol for a randomized controlled trial (RCT) to compare SPO2 to conventional oxygen delivery from cylinders.

## Methods/Design

### Study design

The study is a prospective, randomized, controlled clinical trial comparing solar-powered oxygen delivery to oxygen in compressed cylinders in children under 13 years of age admitted with hypoxemic respiratory illness. The patient flow diagram is shown in Fig. 1.

**Fig. 1 Fig1:**
[figure not shown]
Trial flow diagram. *The trial capacity is two beds with a concentrator and two beds with a cylinder. In case of two patients already enrolled in the same arm, subsequent patients were not enrolled because of the potential inability to randomize to the occupied beds

### Study objectives

The overall objective is to demonstrate the noninferiority of solar-powered oxygen delivery relative to standard oxygen delivery. Specifically, we will compare the length of stay in children hospitalized with acute hypoxic respiratory illness randomized to SPO2 versus cylinder oxygen. The working hypothesis is that the length of stay is not increased in children treated with SPO2 compared to children receiving cylinder oxygen. Secondary outcomes will be compared between groups, including patient-specific outcomes (mortality, duration of supplemental oxygen therapy (time to wean O_2_), proportion of patients successfully oxygenated, and clinical severity scores) and oxygen delivery system indicators (system failures, cost, maintenance and convenience of use).

### Eligibility criteria

#### Inclusion criteria

Inclusion criteria include the following:Age <13 yearsIntegrated Management of Childhood Illness (IMCI) defined severe pneumonia or very severe disease [9]Hypoxemia (peripheral saturation<90 %) based on noninvasive pulse oximetryHospital admission warranted based on clinician judgmentConsent to blood sampling and data collection

#### Exclusion criteria

Exclusion criteria include the following:Outside eligible age rangePeripheral oxygen saturation ≥90 %Suspected pulmonary tuberculosisOutpatient managementDenial of consent to participate in studyTrial inpatient capacity exceeded

The reason for exclusion of patients with pulmonary tuberculosis is for infection control, in order to avoid the risk of transmitting tuberculosis to other patients housed in the study unit. The trial inpatient capacity at each study site is two beds with a concentrator and two beds with a cylinder. In cases where two patients are already enrolled in the same arm, subsequent patients will not be enrolled because of the potential inability to randomize to the occupied beds.

### Study setting

The trial will take place at two hospitals in Uganda: (1) the Jinja Regional Referral Hospital is located in in mid-eastern Uganda, which serves a large catchment area in the Busoga Region, and (2) Kambuga Hospital in Western Uganda, a remote site with limited road access. Both are severely resource-limited hospitals with inconsistent electrical power supply, and both were using oxygen from cylinders and concentrators at the time of study planning. Uganda has a high burden of child mortality and pneumonia: the under-five mortality rate in 2008 was 135 deaths per 1000 (19^th^ highest rate worldwide), and pneumonia is the fourth leading cause of mortality in Ugandan children under five (11 %) [1].

### Treatment groups

Children will be randomly assigned to receive oxygen using either SPO2 or cylinder oxygen in a 1:1 ratio.

The intervention arm is oxygen from a solar-powered concentrator. The SPO2 systems, which are built in Jinja and Kambuga, consist of photoelectric panels (80 W or 175 W panels, Solarworld, Freiburg, Germany), charge controller (FLEXmax 80, OutBack Power, Arlington, WA, USA or 40 A/24 V Controller, Steca Elektronik GmbH, Memmingen, Germany), bank of gel batteries (220 Ah/12 V UltraPower gel batteries, Victron Energy BV, Almere Haven, The Netherlands), power inverter (3000 VA/48 V Inverter/Charger or 1600 VA/24 V Inverter/Charger, Victron Energy BV, Almere Haven, The Netherlands) and oxygen concentrator (model 525 KS, DeVilbiss Healthcare LLC, Somerset, PA, USA). The system is designed to run independently of hydroelectric power source (exclusively driven by solar energy), and provide continuous uninterrupted oxygen (up to 5 L/min) throughout both day and night (using energy stored in battery bank). The total cost of each system was approximately US $18,000.

The control arm consists of oxygen in a cylinder with flow regulator, tubing and nasal prongs or mask for delivery to the patient. Cylinders (pressure, capacity) can be purchased from commercial suppliers in Uganda (Oxygas, Kampala, Uganda) at a cost of US $200 and are refillable at a cost of US $14. In addition, a regulator (US $200) is needed. On average, one pediatric patient with pneumonia will consume approximately 1-6 cylinders of oxygen during the course of hospitalization for pneumonia. In order to have a reliable supply of oxygen, given procurement and transport times, we estimate that six cylinders need to be stocked on the hospital premises.

### Randomization method

Block randomization by study site will be employed, using a computer-generated list. Treatment allocation will be kept in sequentially numbered, sealed, opaque envelopes, which will be drawn for each randomized participant. We will retain all envelopes and records for quality-monitoring purposes.

### Outcome measures

Length of stay will be the primary outcome. A standardized and objective decision rule will be used for hospital discharge. All of the following criteria will be required for discharge: (1) off oxygen for at least 24 hours (requires saturation ≥90 % on room air); (2) absence of fever for 24 hours; (3) vital signs stable; and (4) drinking and/or breastfeeding well.

Several secondary outcomes will be recorded. Patient-specific outcomes will be measured in each group: mortality, proportion of patients successfully oxygenated, duration of oxygen therapy, and clinical severity score. The proportion of patients successfully oxygenated will be defined as the number of patients who achieve a saturation ≥90 % for ≥12 hours after initiating oxygen therapy. The clinical severity scores used will be the previously published and validated Lambaréné Organ Dysfunction Score (LODS) [10] and the Respiratory Index of Severity in Children (RISC) [11].

Oxygen delivery system variables will include direct costs (capital investment, operating costs, system maintenance, *etcetera*), details of maintenance needs, convenience of use of the systems and proportion of patients for whom the delivery system failed. System failure will be defined as inadequate oxygen production to meet patient needs for any reason. Examples would include battery failure for SPO2 or out-of-stock cylinder oxygen.

### Safety

Oxygen therapy is known to be a life-saving intervention, and this study will improve hospital capacity for the treatment of hypoxemic children. While patients will be randomized to one of two possible oxygen delivery systems, there are no risks, and benefits include potentially life-saving access to oxygen, regardless of delivery modality. Study participants will be managed at the Jinja Regional Referral Hospital according to national guidelines and local clinical practices. Outcome assessment in the study will not pose any risk to the study participants.

Adverse events, defined according to Good Clinical Practice (GCP) guidelines as any untoward event occurring in a study participant, will be logged prospectively and tabulated at the end of the study, disaggregated by study arm. Severe adverse events, defined as those adverse events that prolong hospitalization or lead to permanent disability or death, will be reported to regulatory authorities in an expedited manner and reported separately in the safety analysis.

This study involves hypoxemic patients with severe pneumonia or very severe disease, and the mortality is expected to be high because of the underlying illness. Mortality among patients receiving SPO2 will to be interpreted in comparison to patients receiving O_2_ by standard method (cylinders).

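### The severe adverse event definition omits life-threatening events, so one that neither lengthens the stay, disables nor kills is not expedited in either arm

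*Protocol article*

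**What the plan says.** The Safety section of the protocol article sets up two tiers.

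- All adverse events: "Adverse events, defined according to Good Clinical Practice (GCP) guidelines as any untoward event occurring in a study participant". These "will be logged prospectively and tabulated at the end of the study, disaggregated by study arm".
- Severe adverse events: "Severe adverse events, defined as those adverse events that prolong hospitalization or lead to permanent disability or death". These "will be reported to regulatory authorities in an expedited manner and reported separately in the safety analysis".

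On risk, the same section says that "there are no risks, and benefits include potentially life-saving access to oxygen".

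The Outcome measures section treats loss of oxygen supply as something that may happen: "System failure will be defined as inadequate oxygen production to meet patient needs for any reason". It gives one example for each arm: "Examples would include battery failure for SPO2 or out-of-stock cylinder oxygen". The outcome derived from this is the "proportion of patients for whom the delivery system failed". Under Secondary outcomes, that proportion is compared between arms in the same way as mortality, by chi-squared or Fisher's exact test.

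**The concern.** Each of the three criteria for a severe event looks at how things turned out. None looks at the danger at the time. An event that put a child's life at immediate risk, but was reversed without lasting harm or a longer stay, is treated for reporting purposes like any minor adverse event.

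This matters here because the trial compares two ways of supplying oxygen to children with saturation below 90 %, and the reliability of supply is itself under study. The Safety section expects high mortality from the underlying illness. The Discussion describes hospitals without reliable access to intensive care, intubation or ventilation, and expects the energy available to the solar system to vary with sun and weather. An interrupted supply could plausibly endanger a child at once in either arm. Prompt notice to the authorities is most useful for such near misses, and the definition does not require it.

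The statement that there are no risks points the same way. It sits badly beside an outcome that counts children whose oxygen needs were not met.

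**Working it through.** No arithmetic applies. The check applies the stated definition to the possible courses of one event, taking a delivery failure that endangers a child in either arm.

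**Inputs**

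- Criteria for a severe event (Safety): prolonged hospitalization, permanent disability, death.
- Route for severe events (Safety): expedited to the authorities and reported separately.
- Route for other adverse events (Safety): logged prospectively, tabulated by arm at study end.
- System failure (Outcome measures, Secondary outcomes): counted per patient in both arms and compared between them.
- Rate of system failure: not given anywhere in the article.

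**Application**

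| Course after the failure | Criterion met | Expedited and reported separately? | Logged, tabulated by arm, counted as system failure? |
|---|---|---|---|
| (a) Child dies | Death | Yes | Yes |
| (b) Permanent disability | Disability | Yes | Yes |
| (c) Rescued, stay lengthened | Prolonged hospitalization | Yes | Yes |
| (d) Rescued, no longer stay, no disability | None | No | Yes |

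The gap is case (d) only. A life-threatening event that is not a delivery failure follows the same pattern, except that the system-failure outcome does not count it.

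**Does the prolongation criterion close the gap in practice?** Not reliably. Whether one child's stay was lengthened by one event is a counterfactual judgment. The pilot stays quoted under Sample size calculations average 2.6 days with a standard deviation of 2.1. Discharge depends on several conditions together, including 24 hours off oxygen and 24 hours without fever, so a short interruption early in the admission may leave the discharge day unchanged. Where it does change the day, that may become clear only near discharge, and the clinicians judging it are unblinded. Danger to life can be judged when the event occurs.

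**Does the reference to Good Clinical Practice close it?** No. In the text it is attached to the definition of adverse events. Severe events are defined in the article's own words, by the three criteria.

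**Is this only a detail left to a fuller document?** No. The article states a rule and lists its criteria. The point concerns what that list excludes.

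**The case against.** The strongest case on the other side is that little is lost.

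- **Capture and comparison are intact.** Every adverse event is logged and tabulated by arm, and every delivery failure also enters a secondary outcome with a planned test between arms. This stands. A reader might infer that rescued failures vanish from the safety data or from the comparison by arm, and the documents do not support that. Only expedited reporting and separate reporting as severe are missing.
- **Many rescued failures are expedited.** Those in cases (b) and (c) meet the definition. This also stands. It would be wrong to read the rule as excluding every rescued failure.
- **Failures would be visible as they happen.** The trial is unblinded, each site has two beds per arm, and logging is prospective, so staff would see an empty cylinder or a stopped concentrator. This stands as far as local staff are concerned. Whether anyone reviews accumulating events during the trial is something an article may leave to the full protocol, so one cannot infer that failures go unseen until recruitment ends. Local awareness is nevertheless not the same as a duty to report promptly to the authorities.
- **The hazard is not specific to the solar system.** The article gives a failure example for each arm and nowhere calls supply failure the main hazard of the intervention. A reader might infer this, but the text does not say it. The point is therefore put for both arms.
- **The sentence about no risks is loose wording.** It can be read as referring to randomization between two ways of giving oxygen, and it changes no procedure or analysis. That is fair, but the sentence still conflicts with the system-failure outcome and is easily corrected.

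**Conclusion.** The point holds in a limited form. The stated definition omits life-threatening events. A life-threatening event in either arm that leads to neither a longer stay, permanent disability nor death is therefore recorded but neither expedited nor reported separately as severe.

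Its size cannot be computed. The article gives no rate of system failure, and no share of failures that would be life-threatening yet resolve without a listed consequence. Any count per arm would rest on invented rates. The primary outcome, power, sample size and planned comparison of system failure between arms are unaffected.

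The conclusion assumes that the article's definition is the one in force, and that some delivery failures can endanger a child's life without a listed consequence. The second assumption is a judgment from the population and setting described, not a statement in the text. The change is worth making because the gap is in a stated rule, the correction is small, and recruitment was still under way according to Trial status.

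**What to change.** In the Safety section and on the reporting form:

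1. Add events that are life-threatening to the three criteria for a severe adverse event.
2. State that this includes a failure of oxygen delivery, in either arm, that places the child at immediate risk of death, even if the child is rescued.
3. Reconcile the sentence saying there are no risks with the system-failure outcome, for example by acknowledging that either supply may fail.

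No new data collection is needed for delivery failures, since they are already recorded, and no analysis of the primary outcome changes. The cost is additional expedited reports. These may be more than a few: every participant is hypoxemic with severe pneumonia or very severe disease, so a general life-threatening criterion will also take in deterioration from the illness itself. The change concerns reporting only and alters no part of clinical care.

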### Ethical considerations

The Makerere University School of Biomedical Sciences Research and Ethics Committee (SBS-REC, # SBS 139), together with the University Health Network Research Ethics Board (UHN REB, # 13-6168-AE) of the University of Toronto have reviewed and approved the study protocol. The Uganda National Council on Science and Technology (UNCST, # SS 331) has also approved the study.

Written informed consent will be obtained from the caregivers of all children that will participate in the study. The consent has been translated into local languages (Luganda, Lusoga and Rukiiga). Illiteracy is common in the study area, requiring adaptation of the consent process. For those who do not know how to read and write, an independent witness will be present during the informed consent process and will sign the consent form as a witness. The parent themselves will affix a thumbprint to the consent form. Assent will be solicited for patients above 8 years of age.

### Sample size calculations

We will enroll a total of 130 patients. This sample size was calculated as follows. A 1:1 ratio of patients will be assigned to SPO2 or control (cylinder O_2_). We consider a 1-day prolongation of hospital stay to be clinically significant (noninferiority margin). Using pilot data from a prospective study at Jinja Regional Referral Hospital, 69 patients with hypoxic pneumonia had a mean (standard deviation) length of stay of 2.6 (2.1) days (unpublished data). By standard calculations for normally distributed data, 57 patients in each group will provide 80 % power to demonstrate noninferiority of SPO2 relative to oxygen by cylinder at α = 0.05 (one-sided). This sample size was increased by 15 % to account for a probable non-Gaussian distribution of the data [12].

### Primary analysis

Length of stay (in days) will be coded as a whole number (continuous variable). Difference in length of stay between groups will be compared using the nonparametric method of Hodges and Lehman. If the *a priori* noninferiority margin (Δ = 1 day) is below the lower limit of the 95 % confidence interval for the median of differences, the trial will conclude that SPO2 is noninferior to cylinder oxygen. In order to account for all patients randomized (“intention-to-treat” analysis), we will perform sensitivity analyses to account for missing data due to mortality, study withdrawal, and transfer to another facility. A *per protocol* population (non-fatal cases discharged home from hospital) will be used to assess the robustness of the primary result (non-inferiority). Details of the sensitivity analyses will be included in a Statistical Analysis Plan, which will be closed as early as possible in the conduct of the trial.

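### Whole-day coding with a strict Hodges-Lehmann limit rule makes the 1-day noninferiority test very conservative, so the planned 80 % power is not assured

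*Protocol article*

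**What the plan says.** Under Primary analysis, the protocol article fixes three things.

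- Coding: "Length of stay (in days) will be coded as a whole number (continuous variable").
- Method: "Difference in length of stay between groups will be compared using the nonparametric method of Hodges and Lehman".
- Decision: noninferiority is concluded if the 1-day margin "is below the lower limit of the 95 % confidence interval for the median of differences". The comparison is strict, and equality is not mentioned.

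Under Sample size calculations, the margin is given as "We consider a 1-day prolongation of hospital stay to be clinically significant (noninferiority margin"). The pilot input is "69 patients with hypoxic pneumonia had a mean (standard deviation) length of stay of 2.6 (2.1) days". The number per group is derived "By standard calculations for normally distributed data": "57 patients in each group will provide 80 % power to demonstrate noninferiority of SPO2" at one-sided 5 %. It is then raised by 15 % for non-Gaussian data, to 130 in total (65 per arm). The Primary analysis section leaves the details of the sensitivity analyses to the statistical analysis plan. The coding, the method and the decision rule are stated in the article itself.

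**The concern.** The Hodges-Lehmann estimate and its limits are taken from the ordered pairwise differences between arms. If every stay is a whole number, so is every difference, and the limit can be 0 or 1 but nothing between. The margin then sits exactly on a possible value of the limit, and a strict comparison moves the real hurdle from 1 day down to 0. The sample size was worked out as if length of stay were continuous, so it does not reflect this. SPO2 could be truly equivalent, or longer by a few hours that the sponsor would regard as harmless, and the trial could still fail because of rounding.

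**Working it through.** **1. The plan's own figure.** Inputs from Sample size calculations: SD 2.1, margin 1 day, one-sided 5 %, power 80 %.

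n = 2 × 2.1² × (1.645 + 0.842)² / 1² = 8.82 × 6.185 = 54.6, so 55 per group (56 with the t distribution). The plan has 57, within two patients. Then 114 × 1.15 = 131.1, against 130. At one-sided 2.5 %, 8.82 × (1.960 + 0.842)² = 69.2, so 70 per group. The difference, 2 × (70 − 55) = 30, matches the saving given in the Discussion. The sample size is therefore sound for a continuous, normal outcome.

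**2. What the rule becomes.** I read it as: upper limit for SPO2 minus cylinder below 1 day. With the signs reversed it is the mirror image. There are 65 × 65 = 4,225 pairwise differences. The standard error of the rank count is √(4,225 × 131 / 12) = 214.8. The one-sided 95 % upper limit is about the 2,467th ordered difference, since 4,225/2 + 1.645 × 214.8 ≈ 2,466. With whole-day data, a limit below 1 requires at least 2,467 / 4,225 = 58.4 % of differences to be 0 or less.

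**3. Why power depends on ties.** If the arms are identical and a share t of the pairs is tied, the expected share of differences at 0 or less is (1 + t)/2. Its standard error is about 214.8 / 4,225 = 5.1 %. For 80 % power, (1 + t)/2 must be about 0.584 + 0.842 × 0.051 = 0.627, so t must be about 25 %. Tie rates in the simulated shapes:

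- negative binomial 15 %: (1 + 0.15)/2 = 57.5 %, just short of 58.4 %, so power is under one half (simulated 46 %);
- lognormal 21–22 %: 60.5–61 %, moderate power;
- shapes with a 1-day minimum 24–35 %: 62–67.5 %, power from just under 80 % to the mid-nineties.

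**4. Simulation.** 65 per arm, mean 2.6, SD 2.1, one-sided 5 %, strict rule, 1,000–2,000 trials per cell. Stays were coded by rounding, ceiling or floor. The shapes are assumed, because the article gives only mean and SD.

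| Shape | No difference: whole days | Unrounded | True +0.25 day: whole days | Unrounded |
|---|---|---|---|---|
| Gamma | 52–58 % | 95–97 % | 22–24 % | 82–84 % |
| Lognormal | 64–70 % | about 99 % | 25–29 % | 94 % |
| 1-day minimum (gamma, lognormal) | 78–97 % | over 99 % | 30–81 % | 98 % or more |

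A rounded normal shape gave 37 % at no difference, against 84 % unrounded.

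At a true 1-day prolongation the strict rule passed 0–0.3 % of trials; unrounded data gave 4.3–5.7 %. Success under whole-day coding falls to about 5 % near a true prolongation of 0.5 day for gamma and lognormal. For a 1-day minimum plus gamma with ceiling or floor coding it is about 39 % at 0.5 day and 3–4 % at 0.75 day.

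With the two-sided 95 % interval named in the Primary analysis section, power at no difference is about 39–58 % (gamma, lognormal) and 66–93 % (1-day minimum).

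**The case against.** **The discharge rule favours the better case.** Outcome measures requires at least 24 hours off oxygen before discharge, and every enrolled child is hypoxemic. Discharged children should therefore not have stays under 1 day, yet the matched gamma puts 23 % of stays there and the lognormal 16 %. This stands: with a 1-day minimum, power at no difference is about 78–97 %, so it is wrong to say that the stated power cannot be reached. The comfort is limited. A true difference of a quarter of the margin brings the same shapes down to 30–81 %, and deaths, transfers and withdrawals can still give short stays.

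**Tie handling is normally left to the analysis plan, and whole-number limits presuppose the order-statistic interval.** That is partly right: routines that solve for the limit numerically may land just off a whole number. The decision at 1 day would then depend on the software. The coding and the strict rule are nonetheless stated in the article.

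**The sample size was already inflated by 15 %.** All simulated figures use the inflated 65 per arm.

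**Two stronger readings that a reader might infer do not hold.**

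- That the false-positive rate is many times 5 %. It would be about 50–97 % for the gamma, lognormal and 1-day-minimum shapes if a limit of exactly 1 day counted as success. The article does not say that, and its strict rule excludes it.
- That the margin plays no role and any prolongation must be ruled out. If so, success at zero difference would be at most about 5 %, and it is far higher.

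**Conclusion.** The concern holds as a loss of power caused by whole-day coding combined with a strict limit rule. Whole-day data alone are not the defect, since another test on the same data works near the nominal level. That the limits are whole numbers is arithmetic and needs no distributional assumption beyond the usual order-statistic interval. The size of the power loss does depend on the unknown shape of length of stay. The effective margin is well below 1 day: about 0.5 day for gamma or lognormal stays, and up to about 0.75 day for some shapes with a 1-day minimum. The stated 80 % power is missed for several shapes that fit the pilot mean and SD and is reached for others, so it is not assured. The error is on the conservative side. The handling of equality still matters, because the limit fell exactly on 1 day in 4–62 % of simulated trials with no true difference. The literal direction of the rule, and the one-sided 5 % level against a 95 % interval, are separate points to reconcile.

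**What to change.** Define length of stay as discharge date-time minus admission or randomization date-time, in hours divided by 24 and not rounded. Keep Hodges-Lehmann on that scale. In the simulations this restores an error rate of 4.3–5.7 % and gives power of 84 % (normal) or more.

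If clock times cannot be recovered, keep whole days and prespecify one of the following:

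- a tie-corrected (mid-rank) Mann-Whitney test shifted by 1 day: power about 82–100 %, error about 4.1–5.5 %. This stays closest to the planned method;
- a one-sided Welch or bootstrap limit for the mean difference: with Welch, power about 83–87 % and error about 4–5 %. This changes the estimand to the mean, which is the quantity the sample size was based on.

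These are second best, because rounding still distorts differences of part of a day. For the 1-day-minimum gamma at a true 0.5 day, the shifted rank test passed 48 % of trials with rounding and 94 % with ceiling, against 87 % for Hodges-Lehmann on unrounded data.

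In every case, state in advance that a limit equal to 1 day is not success, stop calling a whole-day code continuous, and check power by simulation from the 69 pilot stays.

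The cost is a change of wording and some retrieval of times from charts. The article does not say whether those times were recorded, and recruitment is already under way, so this should be settled without reference to outcomes by arm.
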